## Abstract

**Background:**

Early interventions proved to be able to improve prognosis in acute stroke patients. Prompt identification of symptoms, organised timely and efficient transportation towards appropriate facilities, become essential part of effective treatment. The implementation of an evidence based pre-hospital stroke care pathway may be a method for achieving the organizational standards required to grant appropriate care. We performed a systematic search for studies evaluating the effect of pre-hospital and emergency interventions for suspected stroke patients and we found that there seems to be only a few studies on the emergency field and none about implementation of clinical pathways.

We will test the hypothesis that the adoption of emergency clinical pathway improves early diagnosis and referral in suspected stroke patients. We designed a cluster randomised controlled trial (C-RCT), the most powerful study design to assess the impact of complex interventions. The study was registered in the Current Controlled Trials Register: ISRCTN41456865 – Implementation of pre-hospital emergency pathway for stroke – a cluster randomised trial.

**Methods/design:**

Two-arm cluster-randomised trial (C-RCT). 16 emergency services and 14 emergency rooms were randomised either to arm 1 (comprising a training module and administration of the guideline), or to arm 2 (no intervention, current practice). Arm 1 participants (152 physicians, 280 nurses, 50 drivers) attended an interactive two sessions course with continuous medical education CME credits on the contents of the clinical pathway. We estimated that around 750 patients will be met by the services in the 6 months of observation. This duration allows recruiting a sample of patients sufficient to observe a 30% improvement in the proportion of appropriate diagnoses.

Data collection will be performed using current information systems. Process outcomes will be measured at the cluster level six months after the intervention. We will assess the guideline recommendations for emergency and pre-hospital stroke management relative to: 1) promptness of interventions for hyperacute ischaemic stroke; 2) promptness of interventions for hyperacute haemorrhagic stroke 3) appropriate diagnosis. Outcomes will be expressed as proportions of patients with a positive CT for ischaemic stroke and symptoms onset <= 6 hour admitted to the stroke unit.

**Discussion:**

The fields in which this trial will play are usually neglected by Randomised Controlled Trial (RCT). We have chosen the Cluster-randomised Controlled Trial (C-RCT) to address the issues of contamination, adherence to real practice, and community dimension of the intervention, with a complex definition of clusters and an extensive use of routine data to collect the outcomes.

## Background

Stroke is the third most common cause of death in developed countries [1]. In 80% of cases stroke is ischaemic (caused by thrombotic or embolic occlusion of cerebral artery) [2] the remainder are caused by intracerebral or subarachnoid haemorrages.

Around 10% of all people with acute ischaemic stroke will die within 30 days of stroke onset, while 50% of the survivors will experience some level of disability after 6 months [3].

As early effective interventions proved to be able to improve prognosis [1], implementation of an evidence based pre-hospital stroke care pathway may be a method for achieving early identification of symptoms, and organised timely and efficient transportation towards appropriate care. Clinical pathways have been indicated with different names: care pathways, critical pathway, critical path method, and Care Maps(tm) [4]. We adopted "clinical pathway" to indicate a document targeted to all emergency service personnel (dispatchers, physicians, nurses and any other professionals, such as ambulances drivers) involved in the management of a suspect acute stroke from pre-hospital to emergency phases.

A systematic review on the adoption of in-hospital clinical pathways suggested that the currently available evidence is insufficient to support routine implementation of care pathways for the hospital management of acute stroke or stroke rehabilitation [5]. Therefore there is still uncertainty about the effectiveness of clinical pathways to achieve earlier interventions for stroke patients in pre-hospital setting. We are performing a systematic review on the effectiveness of clinical pathways in pre-hospital field and we also decided to design the present study. The results of the study will be the basis to decide about the widespread implementation of the clinical pathway in the whole region.

Within Lazio, the region with 5,302,302 inhabitants in which the capital city of Rome is located, the emergency medical services (ES) are accessible by dialling "118" with automatic connection to the nearest dispatch facility. The emergency network is organised in three levels of complexity. The basic level involves emergency rooms for first aid; the first level is equipped for mild-severe diagnosis and the second level for the most severe urgency. These services are in a number and a geographical disposition to grant the required assistance in emergency (see figure 1). Calls for interventions are answered by ES dispatchers who activate the nearest ambulance unit. The Basic Life Service (BLS) facilities are superior in number than the Advanced Life Services (ALS) and are commonly forwarded for the suspected stroke patients. Nowadays, BLS are compelled by law to deliver patients to the nearest emergency hospital. There, medical doctors provide the assessment of patients conditions and diagnosis and decide about referral to appropriate facility. The provision of Computerised Tomography (CT) to confirm the diagnosis of stroke, and the transportation of patients to their final destination, may require some times. With the actual organization of system, the process from the emergency call to the admission to the stroke unit may take from several hours up to days.

**Figure 1 F1:**
[figure not shown]
Territorial distribution of the entities enclosed in the study.

The availability of effective early interventions for stroke, calls for reengineering these procedures.

The need for prompt diagnosis and referral requires a that more responsibility is placed on nurses (active in the BLS) who should be trained to recognize early symptoms and should be empowered to contact ES in order to identify the appropriate level of care required, and to transport patients directly to stroke units.

An evidence-based clinical pathway was developed with the methods adopted by the most qualified guidelines development agencies (such as Scottish Intercollegiate Guidelines Network, National Institute for Clinical Excellence and the Italian National Plan for Guidelines Development-PNLG) with the involvement of the emergency health workers in the expert panel, and we decided to evaluate its effectiveness in standardising and improving the procedures in pre-hospital (ES) and emergency (ER) setting, before considering its widespread adoption in our region.

The cluster randomised trial design is indicated in assessing the effectiveness of complex interventions [6] and it allows comparisons of alternative strategies such as guidelines versus conventional educational methods of influencing doctors' management of a particular problem. In our study randomization at cluster level is not only indicated but also necessary to avoid hindrance to the normal activity of the services. We, therefore, adopted as unit of randomization the whole teams of ER or ES stations to avoid contamination.

We present the protocol of study that compares the adoption of an evidence-based prehospital pathway versus current practice.

It is our intention to describe the methodology of the study in the present publication in order to ensure independence of the results and to stimulate criticism and suggestions from the journal readers. The protocol has been presented in several international conferences to share our initiative with the scientific community and to collect their comments and ideas.

As we are aware of the many limits and peculiarity of this study design we believe that lessons on how to deal with complex intervention in the difficult environment will be the added value of the present study.

## Methods/design

### Participants

We identified all the emergency services referring to the two stroke units presently available in Rome (figure 1). There were 47 entities comprising 18 emergency rooms and 29 emergency service stations (52 ambulances) from which we created 20 clusters. The criteria for cluster creation was grouping together the services sharing personnel and/or referring patients each other (figure 2-table 1).

**Figure 2 F2:**
[figure not shown]
**Flow chart of randomization procedure. **Overall we had 20 units of randomization (cluster) of which 10 are couples composed of one ES+1ER on the basis of closeness (usually the ES is situated in the same place of the ER, or systematically refers patients in the same closest ER); 6 are ES and 4 are ER which could not be matched.

**Table 1 T1:** Availability of ambulances and organization of structures in the study area, as reported April 2005.

**Place/Area**	**Emergency Medical Services (ES)**	**Emergency room (ER)**	**Notes**
**Viterbo**			
Viterbo	*Call Center *with Medical Doctors	ER level I	
Montalto di Castro	Medical doctors (h12 closed for holidays)	-	
Tarquinia	Only nurses	ER first aid	Staff sharing ES/ER
Tuscania	Only nurses (h12)	ER first aid	
Vetralla	Medical doctors	-	
Ronciglione	Only nurses	-	Staff sharing ES/ER
Civita Castellana	Only nurses	ER first aid	Staff sharing ES/ER
Orte	Medical doctors	-	
Monte Fiascone	Only nurses	ER first aid	Staff sharing ES/ER
Acquapendente	Medical doctors	ER first aid	Staff sharing ES/ER
**ASL FR**			
Anagni	1 full staffed ambulance + 1 BLS	ER first aid	
Alatri	1 full staffed ambulance + 1 BLS	ER first aid	
Fiuggi	1 ALS – ambulances with medical doctors (4)	-	
Ferentino	1 ALS – ambulances with medical doctors (8)	-	
Frosinone	*Call Center *with medical doctors(8)	ER level I	
Ceccano	2 BLS	ER first aid	
Veroli	1 BLS	-	
Ceprano	2 BLS	-	
Sora	1 full staffed ambulance + 1 BLS	ER first aid	
Isola liri	2 BLS	-	
Atina	1 ALS – ambulance with medical doctor (5)	-	
Pontecorvo	1 First level (staffed for most severe conditions)+ 1BLS	ER first aid	
Cassino	2BLS (only inter-hospital transfer)	ER level I	
**ASL RMG**			
Tivoli	2 BLS	ER level I	A new ER will be opened (during the study period)
Monterotondo	1 BLS	ER first aid	ES and ER randomized independently
Palombara	1 BLS	-	
Palestrina	1 BLS	ER first aid	ES and ER randomized independently
Colleferro	1 full staffed ambulance(h12) + 2 BLS	ER first aid	ES and ER randomized independently
Valmontone	1 BLS	-	
Subiaco	1 BLS	ER first aid	
Olevano Romano	1 BLS	-	
Lunghezza	1 ALS – ambulances with medical doctors (4)	-	
Arsoli	1 BLS	-	
Montelanico	1 BLS	-	
**ASL RMA**			
S. Giacomo	full staffed ambulance – ambulances with medical doctors	ER level I	ES and ER randomized independently
Nomentano	Red Cross (as ALS)	-	
Arno-Treviso	3 BLS + 1 full staffed ambulance – ambulances with medical doctors	-	
Addolorata	3 BLS + 1 ALS – ambulances with medical doctors	-	
Marcigliana	1 BLS	-	

Participants are all the workers belonging to the services enclosed in the study (enclosing the ambulances' drivers).

About 152 physicians, 280 nurses, 50 drivers will be trained on the contents of the clinical pathway. We estimated that around 750 patients will be met by the services in the 6 months of observation.

### Interventions

Participants in the intervention arm will be trained on the content of the clinical pathway and will be given the clinical pathway itself for consultation and discussion in groups.

The clinical pathway is based on available evidence based pre-hospital and emergency interventions for suspected stroke patients.

It consists of the following main points:

- ES dispatcher uses a short form of Cincinnati pre-Hospital Stroke Scale (CHSS) to identify suspected stroke patients during the telephone call;

- ES health workers confirm diagnosis by CHSS on the scene;

- patients are provided CT and referred to appropriate care.

A group of trainers from the expert panel that developed the clinical pathway, and composed of:

- an ES medical doctor

- anaesthesiologist working on helicopter emergency unit

- two neurologists working in stroke unit

- a physician working in an emergency department

- a neurosurgeon

- two epidemiologist and evidence-based medicine expert

trained a group of health workers selected from all the entities participating in the intervention arm study to act as "facilitators" for peer education. The facilitators trained their colleagues in the workplace with the help of audiovisual materials produced by the teachers themselves.

At least one representative of the teachers' group took part in the meetings on the workplace to support groups' discussion and to answer possible questions. As a result of the training sessions every person working in any entity participating in the intervention arm of the trial have been trained on the content of the pathway.

No interventions will be implemented in the control group.

### Objectives

The objective of this cluster randomised controlled trial is to evaluate the effectiveness of pre-hospital and emergency clinical pathway for patients with suspected stroke in: improving early identification of stroke, promoting appropriate triage coding, achieving coherence between diagnosis, interventions and referral.

### Outcomes

The outcomes relate to organizational aspects (transportation to the appropriate hospital, accurate diagnosis and interventions, timely treatments) and will be measured as:

#### Primary outcome

- proportion of patients with a positive CT for ischaemic stroke and symptoms onset <= 6 hour admitted to the stroke unit

#### Secondary outcomes

- proportion of patients with a positive CT for hemorrhagic stroke and symptoms onset <= 6 hour admitted to a neurosurgical ward

- proportion of patients with a positive CT for hemorrhagic or ischaemic stroke or symptoms onset >6 hour admitted to the nearest hospital

- proportion of ICD9CM code for stroke in emergency setting confirmed in the hospital discharge data

- proportion of patients with stroke confirmed by CT results

- proportion of patients with ischaemic stroke receiving treatment within 6 hour of symptoms onset

All the outcomes will be reported at cluster level and will be cross-checked by the integration of data from the available information systems.

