### Sample size

We calculated the sample size, i.e. the duration of recruitment, keeping into account the number of emergency calls and the number of emergency room admissions for suspect stroke.

For the ES the mean number of patients per 19 clusters was about 50 (see figure 2). The estimate percentage of correctly transferred patients, based on the Information System of Emergency Rooms in 2003, is 47%. We assumed an intra cluster correlation of ICC = 0.05. Under this assumption we decided 6 months duration, i.e. 25 patients per cluster, to obtain a power of 95% to detect a difference of 50% in rates between the two groups, i.e. reaching about 70% of correctly transferred patients in the treated group, with a = 0.05.

For the emergency rooms the mean number of patients per 14 clusters was about 110. The estimate of correctly transferred patients, based on the Information System of Emergency Rooms in 2003, is 14%. We assumed an intra cluster correlation of ICC = 0.05. Under this assumption and with a duration of 6 months, i.e. 55 patients per cluster, to obtain a power of 95% to detect a difference of 150% in rates between the two groups, i.e. reaching about 35% of correctly transferred patients in the treated group, with a = 0.05.

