### Stopping rules

The nature of the intervention to be experimented prevented us from identifying specific stopping rules and we could only commit ourselves to submitting any possible problems to the ethical committee. The core of the pathway consists of transferring patients likely to benefit from complex interventions to specialized structures, rather than providing them with minimal assistance in the nearest hospital. This means that health workers belonging to experimental clusters may need to transfer patients for longer distance than they used to do. The risks we can foresee are unexpected events during transportation and troubles deriving from the unavailability of ambulances. Health workers have been warned to promptly report any kind of problems to the study coordinator.

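### As printed, the second secondary outcome includes every early stroke covered by the primary and first secondary outcomes, so its early-stroke part moves against them

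*Protocol article*

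**What the plan says.** The article lists three outcomes about where patients are admitted.

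- Primary outcome: "proportion of patients with a positive CT for ischaemic stroke and symptoms onset <= 6 hour admitted to the stroke unit".
- First secondary outcome: "proportion of patients with a positive CT for hemorrhagic stroke and symptoms onset <= 6 hour admitted to a neurosurgical ward".
- Second secondary outcome: "proportion of patients with a positive CT for hemorrhagic or ischaemic stroke or symptoms onset >6 hour admitted to the nearest hospital".

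The first two join CT result and onset time with *and*. The third joins them with *or*.

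The Outcomes section gives the purpose: "The outcomes relate to organizational aspects (transportation to the appropriate hospital, accurate diagnosis and interventions, timely treatments". Under Stopping rules, the core of the pathway is described as "transferring patients likely to benefit from complex interventions to specialized structures, rather than providing them with minimal assistance in the nearest hospital". No section limits the third definition to late presenters, and none says whether a higher or a lower value is desirable.

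**The concern.** The three definitions look meant to divide patients by appropriate destination. As printed they do not, because the third contains all the patients of the first two. One early stroke patient can then be scored in opposite senses by two outcomes that are both introduced as measures of reaching the appropriate hospital.

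The outcomes are to be extracted from existing information systems, so the logical operator in the definition decides who is counted. A query that follows the text would pool early strokes moved to specialist care with patients for whom the nearest hospital may be the intended destination. A fall could then reflect nothing more than success on the primary outcome. The Background says the results will inform the decision on region-wide adoption, so a contradictory referral measure would be awkward to explain.

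**Working it through.** **The plan's own figures.** The article states no expected value for this outcome. Its only calculation is the power for correctly transferred patients (Sample size), given as 95% in each setting with an ICC of 0.05. Taking a two-sided 5% level and equal arms:

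- Emergency services: design effect 1 + 24 × 0.05 = 2.2; effective patients per arm 19 × 25 / 2 / 2.2 = 108.0; 47% against 70% gives power 93.5%.
- Emergency rooms: design effect 1 + 54 × 0.05 = 3.7; effective patients per arm 14 × 55 / 2 / 3.7 = 104.1; 14% against 35% gives power 94.6%.

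Both are close to the stated 95%. The rate pairs can therefore be taken as the planned effects, and none of this depends on the second secondary outcome.

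**Step 1: read the definitions side by side.** The nearest hospital is taken not to house the stroke unit or neurosurgical ward.

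| Patient | Primary | First secondary | Second secondary, as printed |
|---|---|---|---|
| Ischaemic, ≤6 h, nearest hospital | failure | – | numerator |
| Ischaemic, ≤6 h, stroke unit | numerator | – | denominator only |
| Haemorrhagic, ≤6 h, nearest hospital | – | failure | numerator |
| Haemorrhagic, ≤6 h, neurosurgical ward | – | numerator | denominator only |
| CT-positive, >6 h, nearest hospital | – | – | numerator |
| CT-negative, >6 h, nearest hospital | – | – | numerator |

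The first four rows show the overlap and the opposed scoring. They need no assumption beyond the one about the nearest hospital.

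**Step 2: effect on the whole proportion.** Let *e* be the share of this denominator who are early ischaemic strokes, *p* the share of them admitted to the stroke unit (the rest being at the nearest hospital), and *q* the share of everyone else admitted to the nearest hospital.

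Outcome = e(1 − p) + (1 − e)q

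If q is the same in both arms it cancels, and the change is −e × (p treated − p control). The article gives neither e nor q. I take e from 20% to 50% and q = 90%, both as assumptions. For p I use the Sample size rates as a stand-in.

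| e | 47% to 70% | 14% to 35% |
|---|---|---|
| 20% | 82.6% to 78.0% (−4.6) | 89.2% to 85.0% (−4.2) |
| 30% | 78.9% to 72.0% (−6.9) | 88.8% to 82.5% (−6.3) |
| 50% | 71.5% to 60.0% (−11.5) | 88.0% to 77.5% (−10.5) |

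**Step 3: what would cancel the fall.** The whole proportion stays level if q rises by e × (p treated − p control) / (1 − e). For 47% to 70% this is 0.046 / 0.8 = 5.75 points at e = 20%, 0.069 / 0.7 = 9.9 points at 30%, and 0.115 / 0.5 = 23.0 points at 50%. With e = 20% and q rising from 90% to 100%, the outcome goes from 82.6% to 0.2 × 0.30 + 0.8 × 1.00 = 86.0%, a rise of 3.4 points.

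**Step 4: after the overlap is removed.** The term e(1 − p) drops out. With other patients' destinations unchanged, the change is 0.0 points, whatever the primary effect.

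**The case against.** Several objections have weight.

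- *The net direction is not fixed.* A reader might infer that a working intervention must lower this outcome and so appear harmful. The documents do not support that. Only the early-stroke part is bound to move against the primary outcome, and Step 3 shows that the total can rise. The Background says that "BLS are compelled by law to deliver patients to the nearest emergency hospital", which suggests limited room for q to rise. But that concerns delivery by basic ambulance crews, not final admission, so it does not settle the matter.
- *The slip may not be the word* or. A reader might infer that *and* was intended. It is equally possible that *positive* stands where *negative* was meant. CT-negative patients, or those with late onset, would then form the remainder after the two specialist destinations, and *or* would be correct. Nothing in the article favours either reading.
- *Late presenters are not lost.* The primary outcome already needs onset split at 6 hours, so they can be tabulated separately. The printed outcome pools them but does not prevent separation.
- *The size rests on assumed inputs.* The early share is not in the article. The 47% and 70% are rates of correct transfer in the emergency services, not stated rates of the primary outcome. The Sample size and Discussion sections also attach 47% and 14% to opposite settings, although the two planned differences (23 and 21 points) give similar results here.
- *Overlap with the specialist unit.* Where the nearest hospital has the stroke unit or neurosurgical ward, one patient can count favourably in both outcomes. The article names only two stroke units for 47 entities but does not say how often this would happen.
- *Success is an inference.* No direction is stated for this outcome. Reading it as a measure of appropriate destination follows from the Outcomes section and is reasonable.

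These points limit the claim about size, direction and remedy. None removes the overlap, and no other section resolves it.

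**Conclusion.** The definition is wrong as written. It includes all patients of the primary and first secondary outcomes. Unless the nearest hospital houses the specialist unit, it counts in its numerator early patients whom those outcomes count as failures.

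The size is conditional. If early ischaemic strokes not reaching the stroke unit are at the nearest hospital, and other patients' destinations do not change, the proportion falls by the early share times the primary effect. For assumed shares of 20% to 50% and 47% to 70%, that is about 5 to 12 points, an illustration and not an estimate for this trial.

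The severity is moderate. A reader might infer that the trial's main conclusion is at risk, but the primary outcome is defined separately and the sample size does not rest on this outcome.

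**What to change.** Before any data are analysed, including the preliminary analysis planned at three months, reconcile this definition with the primary outcome and with the aim described under Stopping rules. Make the three referral outcomes mutually exclusive by removing from this denominator the patients who belong to the primary and first secondary outcomes. That step is valid whichever word was the slip.

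The authors must then state which group they intend, for example CT-positive *and* onset over 6 hours, or CT-negative *or* onset over 6 hours. Either is disjoint from the other two outcomes. They differ in whether CT-negative patients are counted, so the choice cannot be left to the programmer. The text should also say which direction is favourable, and how to count a patient whose nearest hospital contains the specialist unit.

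The cost is a revised sentence and the matching data query. CT result, onset time and admission destination are already needed for the primary outcome, so no extra data collection follows and the sample size does not change.

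### The treatment-within-6-hours outcome counts every ischaemic stroke, so patients first seen after 6 hours fail by definition in both arms and dilute the absolute difference and power

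*Protocol article*

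**What the plan says.** The last secondary outcome (Protocol article, Secondary outcomes) is the "proportion of patients with ischaemic stroke receiving treatment within 6 hour of symptoms onset". The 6 hours qualify the receipt of treatment. The patients counted are those with ischaemic stroke, with no limit on time since onset.

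Two parallel outcomes are built differently. The primary outcome is the "proportion of patients with a positive CT for ischaemic stroke and symptoms onset <= 6 hour admitted to the stroke unit", and the first secondary outcome is the "proportion of patients with a positive CT for hemorrhagic stroke and symptoms onset <= 6 hour admitted to a neurosurgical ward". Both put the onset limit on the patients counted. Another secondary outcome includes patients with "symptoms onset >6 hour admitted to the nearest hospital", so late presenters are among the patients the trial observes.

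The intervention is aimed at staff: "Participants are all the workers belonging to the services enclosed in the study" (Participants). Its first step is that the "ES dispatcher uses a short form of Cincinnati pre-Hospital Stroke Scale (CHSS) to identify suspected stroke patients during the telephone call" (Interventions). The article describes no component addressed to the public.

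**The concern.** Someone who calls or walks in eight hours after onset cannot be treated within six, whatever the staff do. Such patients stay in the denominator and add no possible success in either arm. The outcome therefore mixes what the services do after contact, which the pathway targets, with how long patients wait before contact, which it does not.

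The Outcomes section names timely treatment among the things to be measured, and the abstract puts promptness in hyperacute ischaemic stroke first among the areas assessed. This is the only listed outcome that records when treatment is given. If its absolute effect is diluted, a real gain in promptness could be missed or look small.

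**Working it through.** **Inputs.** From Sample size: 19 ES clusters of 25 patients, 47% against 70%; 14 ER clusters of 55 patients, 14% against 35%; ICC 0.05; alpha 0.05 (two-sided assumed); stated power 95% for each. These rates are for correct transfer, not treatment. They serve here only as example success rates among patients who can still be treated in time. The labels ES and ER follow Sample size; the Discussion attaches 14% and 47% the other way round, which does not matter for an illustration.

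**Step 1: reproduce the plan's own figure.** Effective n per arm = clusters × m / 2 / [1 + (m − 1) × ICC], followed by the normal-approximation power for two proportions with pooled variance under the null.
- ES: design effect 1 + 24 × 0.05 = 2.2; effective n = 237.5 / 2.2 = 108; power 93.5%.
- ER: design effect 1 + 54 × 0.05 = 3.7; effective n = 385 / 3.7 = 104; power 94.6%.

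Both are within 2 points of the stated 95%, so the method is a fair basis for the comparison.

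**Step 2: dilution.** Let L be the share of ischaemic strokes first seen after 6 hours, equal in both arms, and s = 1 − L. If success among the rest is p, the all-stroke rate is s × p, so the difference between arms becomes s × (p1 − p0). With a restricted denominator the rates stay at p, but each cluster has only s × m patients. The ICC is kept at 0.05 throughout.

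ES example at L = 50%:
- All strokes: 0.5 × 47% = 23.5% against 0.5 × 70% = 35%, a difference of 11.5 points; effective n 108; power 46%.
- Restricted: 47% against 70%, a difference of 23 points; m = 12.5; design effect 1 + 11.5 × 0.05 = 1.575; effective n = 118.75 / 1.575 = 75.4; power 82%.

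| Late share L (assumed) | ES rates: difference, all strokes | Power, all / restricted | ER rates: difference, all strokes | Power, all / restricted |
|---|---|---|---|---|
| 20% | 18.4 points | 78% / 91% | 16.8 points | 87% / 93% |
| 50% | 11.5 points | 46% / 82% | 10.5 points | 64% / 89% |
| 70% | 6.9 points | 26% / 68% | 6.3 points | 41% / 80% |

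The restricted differences stay at 23 points (ES rates) and 21 points (ER rates).

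**Step 3: relative scales.** The risk ratio is (s × p1) / (s × p0) = p1 / p0, so it stays at 1.49 (ES rates) and 2.50 (ER rates) for any s. The odds ratio does shrink: at L = 50% from 2.63 to 1.75 (ES) and from 3.31 to 2.82 (ER).

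The precision of the risk ratio also suffers. The variance of its logarithm is the sum over arms of (1 − rate) / (n × rate). For ES rates at L = 50%:
- All strokes: 0.765 / (108 × 0.235) + 0.65 / (108 × 0.35) = 0.0474, standard error 0.218.
- Restricted: 0.53 / (75.4 × 0.47) + 0.30 / (75.4 × 0.70) = 0.0206, standard error 0.144.

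**The case against.** **The line may be shorthand.** The abstract speaks of hyperacute ischaemic stroke, and the parallel outcomes apply a 6-hour limit, so a restricted population may have been meant. But the article does not define hyperacute, and an undefined word does not override the outcome as listed. It does suggest that the restricted population was the target, which favours the correction.

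**The effect is not shrunk on the protocol's own scale.** The article expresses its target effects as relative changes (50%, 150%, and 30% in the abstract), and the risk ratio survives dilution when the late share is equal by arm. This stands. A reader might infer that the effect is attenuated on every scale; it is not. What is lost is the absolute difference, the odds ratio and precision.

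**All strokes is a legitimate population measure.** It suits a decision on region-wide adoption. This also stands, and is a reason to keep it as a supportive result.

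**Patient delay may differ between clusters or arms.** A reader might infer that rural stations, Rome and walk-in patients are known to differ. The article has no data on time from onset to contact, so this is conjecture. Stratification by type of cluster partly balances the mix of calls and walk-ins. As a rough check, 750 patients in 20 clusters are 37.5 per cluster. With ICC 0.05 (assumed to apply to late arrival) the design effect is 1 + 36.5 × 0.05 = 2.8. With half of patients late, the standard error of the arm difference in late share is √(2 × 0.25 / (375 / 2.8)), about 6 points. A 10-point imbalance would arise by chance in about one trial in ten. If success among early patients were 20% to 40% (assumed), it would move the outcome by 0.1 × 20 to 0.1 × 40 = 2 to 4 points, variation that a cluster-based confidence interval already allows for.

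**Restriction has its own risk.** A reader might infer that it cannot select patients differently by arm. It can: eligibility would depend on recorded onset, training may change how onset is recorded, and the Discussion admits that registration is sometimes heterogeneous. The article also does not say that its information systems hold call or arrival times. Both points stand and shape the fix. The numerator, however, already needs onset time, and so does the primary outcome.

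**Conclusion.** The concern holds for the denominator. As written, patients first seen after 6 hours are certain failures in both arms, the pathway cannot change that, and the protocol's own parallel outcomes avoid the problem. The absolute difference falls in proportion to the late share. At an assumed 50%, power is about 46% against 82% (ES rates) or 64% against 89% (ER rates), and the restricted version does better despite having fewer patients. The risk ratio is unchanged if the late share is equal by arm, though less precise.

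These sizes rest on an assumed late share of 20% to 70%, on transfer rates standing in for treatment rates, on the cluster counts in Sample size, and on an ICC of 0.05 in both denominators. The direction of the absolute and power results does not depend on the exact share.

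This is one secondary outcome for which the article claims no power. The primary outcome and the sample size are untouched. A reader might also object that the treatment counted is not named, but the Interventions section lists only the pathway's main points, so in a condensed article that is missing detail and no fault.

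**What to change.** Restrict the denominator to patients with ischaemic stroke who present within 6 hours of onset, in line with the primary outcome. Time presentation at first contact (emergency call, or arrival for those who come to the emergency room themselves) where the information systems hold that time, and confirm this before the definition is fixed. Report the proportion among all ischaemic strokes as a supportive result.

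The change takes a sentence or two in the outcome definition and no new data collection if those times exist. Its costs are a smaller denominator and dependence on recorded onset. One rule for missing onset should therefore be fixed in advance and applied in both arms, with the share of missing onset reported by arm. The change reduces the problem without removing it, since a patient first seen minutes before the limit remains a near-certain failure.
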